#### Data management

All participant information, including informed consent forms, interviews on audio files, etc., will be stored separately from study records identified by code number in locked file cabinets in areas with limited access. The original data collection forms are to be stored in numerical order in a secure and accessible place and manner for a period of 10 years after completion of the study. An external research assistant will enter data into the computer and also perform quality control of the database. During and after the study completion, the research group will have access to the full database. Any modifications to data written to the database will be documented in a log book linked to the database. Regular back-ups of the database will be undertaken automatically by the university’s information technology department. The main database, as well as local databases, will be secured with password-protected access systems.

No data monitoring committee will be needed since risks in connection with this study are minimal, there is a fixed target figure for included participants, and no interim analyses are planned. Even so, the research group, and ultimately the research leader, will be responsible for database security and quality.

#### Statistical analyses

Analyses of intervention outcomes and change over time will be made on the basis of the intention-to-treat principle, which means that participants will be analysed on the basis of the group to which they were randomised [45]. Standard adjustment of analyses according to eventual differences between groups at baseline will be made if necessary. After a thorough examination of the characteristics of collected data, the research group will consider different options for handling missing data. One possibility is the imputation method used in the preceding study ‘Elderly Persons in the Risk Zone’ [25,26], where a missing value was imputed with a value based on the median change of deterioration (MCD) between two measuring points (baseline and respective follow-up) of all those who participated at both measuring points. However, other methods of handling missing data will also be considered, and a final decision will be made by the lead researcher in consultation with a renowned statistician. Regardless of the method chosen, sensitivity analyses will be performed to compare the results to complete case analyses [46]. Although it is desirable, no subgroup analyses are predetermined. Instead, a valuation of the quality of collected data will determine if and which of these analyses are possible. Both descriptive and analytical statistics will be used to compare the groups and to measure change over time. Non-parametric statistics will be used in all cases where ordinal data are to be analysed; otherwise, parametric statistics will be used. A *p-*value of 0.05 or less will be considered significant. Statistical analyses will be performed using IBM SPSS Statistics for Windows, Version 22.0 (Armonk, NY, USA: IBM Corp. Released 2013).

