#### Outcomes

Activities of daily living (ADL) is the primary outcome measure [42,43]. Secondary outcome measures are: physical frailty indicators (mobility, strength, balance, cognition, nutrition, fatigue, physical activity, and visual impairment), falls and fear of falls, symptoms, depression, healthcare consumption, self-rated health, life satisfaction, leisure activities, assistive technology, and social support. The outcomes have, to a large extent, been tested for validity and reliability. All outcome measures are to be assessed at baseline and at the 6- and 12-month follow-ups. Details are provided in Table 3.

**Table 3 Tab3:** **Outcome measurements and follow-ups in the RCT part of the promoting aging migrants’ capabilities study**

**Primary outcome**	**Measurement**	**T0**	**T1**	**T2**
		**baseline**	**6-months**	**12-months**
Activities of Daily Living (ADL)	The ADL-staircase	X	X	X
**Secondary outcome**	**Measurement**			
Fatigue	The Mob-T scale	X	X	X
Grip strength	North Coast-dynamometer	X	X	X
Physical activity	Questionnaire	X	X	X
	Physical and domestic activity scale	X	X	X
Balance	The Berg balance scale	X	X	X
Gait speed	Four-meter walking test	X	X	X
Weight loss	The Göteborg Quality of Life Instrument	X	X	X
Cognition	Mini Mental State Examination (MMSE)	X	X	X
Visual impairment	KM-visual acuity chart	X	X	X
Falls	Questionnaire	X	X	X
Fear of falls	Questionnaire	X	X	X
Symptoms	The Göteborg Quality of Life Instrument	X	X	X
Depression	GDS 20	X	X	X
Healthcare consumption	Register data	X	X	X
Self-rated health	SF 36 (one question)	X	X	X
Life satisfaction	Fugl-Meyer -LiSat	X	X	X
Participation/Leisure activities	Questionnaire	X	X	X
Assistive technology	Questionnaire	X	X	X
Social support	Questionnaire	X	X	X

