#### Recruitment, participant timeline, and randomisation

The results of the pilot study preceding this full-size RCT ([name], [name], [name]: Unpublished observations) indicated that the recruitment procedure described in the original protocol for the senior meetings [24] needed to be adjusted to be more effective. Therefore, a plan consisting of three waves of recruitment strategies was adopted. The waves are hierarchical and an appropriate wave was to be added if an antecedent wave was unsuccessful in reaching the target number for inclusion. The first wave implies that participants are drawn at random from official registers in the urban district. All addresses, equally divided between the populations (Finland and the four countries in the Balkan Peninsula), are listed in random order (two separate lists). Based on the sampling lists, participants will be consecutively included in the study until the decided sample size is reached (n≥65 from each population). Letters will be sent to all randomly selected persons asking them to participate in the study. Invited participants also receive a description of the study, how it is to be conducted, and what is expected of those consenting to participate. The letter stresses the fact that participation is voluntary; it is followed by a telephone call about 1–2 weeks later. If no telephone number is to be found in public records, a second letter with a request to make contact by telephone is sent. During the call, the persons will be informed verbally about the study and given the opportunity to ask questions if anything is unclear. They are also asked personally if they would like to participate, while again stressing that participation is voluntary. Everyone who fulfils the criteria for inclusion and decides to participate is randomised by the research assistant after baseline assessment to one of the two groups using sealed, opaque envelopes prepared by an unattached researcher. Participants living together in the same household are allocated to the same group. Wave two is identical to wave one but involves an expansion of the targeted area to also include another adjacent urban district with similar demographics. Finally, wave three entails word-of-mouth promotion through one-chain snowballing [44]. This strategy uses former study participants and key persons in the aforementioned reference groups to facilitate spreading information about the study. Interested persons fulfilling inclusion criteria are invited to contact the operative group for further information and to undergo baseline assessment when appropriate. The third wave also includes local radio station advertisements containing brief information in the participants’ mother tongue on the study and how to contact the operative group. A detailed overview of the planned flow of participants is provided in Figure 1.

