#### Power calculation

The power calculation was based on results gained in the preceding study ‘Elderly Persons in the Risk Zone’ [24], using the Berg balance scale as a basis. The Berg balance scale is one of the secondary outcome variables (range 0–56), with assumed mean values for the intervention and control groups of 32 and 28, respectively (15% difference), and a standard deviation of 8 in both groups. To be able to detect a significant difference between the two groups in a two-sided test with a significance level of 0.05 and 80% power, we need at least 65 persons in each group. Therefore, a total of at least 130 persons will be included.

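### Baseline adjustment is triggered by observed group differences instead of being fixed in advance, which forgoes precision and leaves the analysis open after the data are seen

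*Protocol article*

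**What the plan says.** The Statistical analyses section of the protocol article sets this rule: "Standard adjustment of analyses according to eventual differences between groups at baseline will be made if necessary". It names no covariates, no criterion for a difference that counts, and nobody who decides. The same section plans intention-to-treat comparisons of outcomes and of change over time, with non-parametric methods for ordinal data and parametric methods otherwise. No other section fixes a baseline-adjusted comparison.

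The Outcomes section states: "All outcome measures are to be assessed at baseline and at the 6- and 12-month follow-ups". It also states: "Activities of daily living (ADL) is the primary outcome measure". Under Masking (blinding), participants, professionals and assessors are all unblinded.

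The sample size is for a comparison of two means on the Berg balance scale, a secondary outcome, with assumed means of 32 and 28 and "a standard deviation of 8 in both groups". The Power calculation section concludes that "in a two-sided test with a significance level of 0.05 and 80% power, we need at least 65 persons in each group".

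**The concern.** Allocation is by sealed, opaque envelopes after baseline assessment, so differences between the arms at baseline arise by chance. Their size says nothing about whether a variable predicts outcome, and prediction is what makes adjustment worthwhile. A strongly prognostic variable is worth adjusting for when the arms look alike; a non-prognostic one gains nothing from adjustment when they look different.

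Two things are at stake. The first is precision: the baseline value of each outcome is collected, but the rule uses it only if a difference appears. The second is freedom of choice: deciding on necessity after the data are in, in an unmasked trial whose research group has access to the full database while the study runs, allows the analysis to be chosen with results in view.

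**Working it through.** **Inputs.** From the Power calculation section: difference 32 − 28 = 4, SD 8, standardised difference 4/8 = 0.5, two-sided alpha 0.05, power 80%, 65 per arm. Assumed here, because the article does not give them: the baseline-outcome correlation ρ, shown at 0.3, 0.5 and 0.7; and, for the conditional rule, a trigger of p<0.05 in a baseline t-test.

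**Step 1: the plan's own figure.** n per arm = 2 × (1.96 + 0.8416)² × 8² / 4² = 62.8, so 63 by the normal approximation; the t-test gives 64. The stated 65 is reproduced within 2 participants. Power at 65 per arm is 81.3% (normal) or 80.8% (t-test). This is an unadjusted comparison.

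**Step 2: power by formula.** Power = Φ(0.5 × √(65/2) / k − 1.96) = Φ(2.850/k − 1.96). Here k is the SD of the analysed quantity relative to the raw SD:
- follow-up score only: k = 1
- change score: k = √(2(1 − ρ))
- ANCOVA: k = √(1 − ρ²)

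| ρ | Follow-up only | Change score | ANCOVA | ANCOVA minus change |
|---|---|---|---|---|
| 0.3 | 81.3% | 67.3% | 84.8% | 17.5 |
| 0.5 | 81.3% | 81.3% | 90.9% | 9.5 |
| 0.7 | 81.3% | 95.7% | 97.9% | 2.2 |

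(Differences are taken before rounding.) Since 2(1 − ρ) − (1 − ρ²) = (1 − ρ)², which is never negative, the ANCOVA variance is never above the change-score variance. Nor is it above the follow-up-only variance, since 1 − ρ² ≤ 1. With ANCOVA, the number per arm for 80% power falls from 63 to 58, 48 and 33.

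**Step 3: the conditional rule by simulation.** Normal data, 65 per arm, 200,000 trials under no effect and 100,000 under a 0.5 SD effect for each ρ. The simulation uses t-based tests, so its figures sit slightly below the formula.

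| ρ | Power: never adjust | Power: adjust if baseline p<0.05 | Power: always adjust | Forgone (points) |
|---|---|---|---|---|
| 0.3 | 80.6% | 80.9% | 83.9% | 3.0 |
| 0.5 | 80.8% | 81.8% | 90.2% | 8.4 |
| 0.7 | 80.8% | 82.7% | 97.6% | 14.9 |

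| ρ | Type I error: always adjust | Adjust if baseline p<0.05 | Better of adjusted and unadjusted |
|---|---|---|---|
| 0.3 | 5.0% | 4.7% | 6.3% |
| 0.5 | 5.0% | 4.3% | 7.4% |
| 0.7 | 5.0% | 3.6% | 8.2% |

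**Limits.** The simulation assumes independent participants and no dropout. It ignores the allocation of people in one household to the same group.

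**The case against.** The strongest objection is that the article states no trigger, no correlation and no comparator, so the size of the loss is the reviewer's construction. Much of this stands. The p<0.05 trigger and the correlations are assumptions. If change scores are compared, which the stated interest in change over time would allow, the gain from ANCOVA at a correlation of 0.7 is about 2 points, not 15. The figures are for the Berg scale. The primary outcome is ADL, and entrants must not depend on help in daily activities, which narrows the baseline spread.

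It can also be said that covariate lists belong in an analysis plan that is not shown. That would answer a silence, but the article states a rule, and an analysis plan would have to contradict it to put it right.

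Three stronger readings are tempting and are not supported:
- **That the rule inflates type I error.** Under a fixed pre-test the error rate is below 5%. Inflation needs freedom to report the better result; the article does not exclude that, but does not plan it either.
- **That ADL could not be adjusted.** The article says only that ordinal data will be analysed non-parametrically. Stratified and covariate-adjusted rank methods exist.
- **That leaving out population of origin is an error.** Recruitment uses separate lists for the two populations, but silence on population as a covariate does not exclude it and may be settled in the analysis plan.

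**Conclusion.** The concern holds in a limited form. Tying adjustment to observed imbalance is a poor rule: it responds to chance, leaves room for choice after the data are seen, and forgoes precision from data the trial already collects. Prespecified adjustment has the correct error rate and, for the correlations examined, more power than either unadjusted follow-up scores or change scores.

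The size is uncertain. For the Berg scale it is roughly 3 to 15 points of power against the assumed pre-test rule, and roughly 2 to 18 points against change scores, over correlations of 0.3 to 0.7. The two ranges run in opposite directions: the gain over the pre-test rule rises with correlation, while the gain over change scores falls. For ADL no figure can be given; the gain from its baseline value is probably smaller. The trial is not invalidated, but the sentence should be changed.

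**What to change.** Replace the sentence with: *Between-group comparisons will be adjusted for the baseline value of the outcome and a short list of covariates named in advance (for example population of origin, age and sex), whatever the observed imbalance; unadjusted results will be reported as supportive.*

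Use ANCOVA for continuous outcomes. For ordinal outcomes, including ADL, name a covariate-adjusted ordinal or rank-based method, such as proportional-odds regression or rank ANCOVA; the latter keeps to the non-parametric rule. Fix the list before outcomes are compared by arm.

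The cost is wording only. Baseline values of all outcomes are already collected, age and country of birth are entry criteria, and demographics are part of the baseline assessment. No extra visits or participants are needed.

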#### Study population

The intention is that the study group should comprise as representative a sample as possible of older persons in the urban district who have migrated to Sweden. For pragmatic reasons, particularly considering the need for language resources, we chose to include persons from two of the largest immigrant groups in the targeted urban district, one Nordic country (Finland) and one European region (the Balkan Peninsula, including the countries Bosnia-Herzegovina, Croatia, Montenegro, and Serbia, the populations who share their mother tongue). Persons eligible for the RCT must therefore comply with all of the following criteria for randomisation: born in Finland or any of the selected four countries in the Balkan Peninsula (Bosnia-Herzegovina, Croatia, Montenegro, and Serbia); 70 years of age or older; living in ordinary housing in the urban district; and not dependent on informal or formal help in daily activities. The only exclusion criterion is impaired cognition (Mini Mental State Examination (MMSE) below 80% of administered items [41]).

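### The missing-data method for ADL is to be chosen after the data are examined, and the one method described, a pooled median change, can distort the comparison if dropout differs between arms

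*Protocol article*

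**What the plan says.** The Statistical analyses section sets the timing of the choice: "After a thorough examination of the characteristics of collected data, the research group will consider different options for handling missing data". On who chooses, it says that "a final decision will be made by the lead researcher in consultation with a renowned statistician".

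One method is described. It is introduced by "One possibility is the imputation method used in the preceding study", and in it "a missing value was imputed with a value based on the median change of deterioration (MCD) between two measuring points". The median is that "of all those who participated at both measuring points"; no split by arm is mentioned. The section adds that other methods will be considered, and that a comparison with complete cases will be made whichever is chosen.

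The Data management section says: "During and after the study completion, the research group will have access to the full database". Table 2 gives the masking as non-blind. The Masking section explains why participants, professionals and assessors cannot be blinded; it does not mention the person who selects or runs the analysis.

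Under Outcomes, "Activities of daily living (ADL) is the primary outcome measure", recorded on the ADL-staircase at baseline, 6 and 12 months. Under Study population, entrants must be "not dependent on informal or formal help in daily activities". The article gives no dropout rate and no expected distribution of ADL change.

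**The concern.** Two features combine. First, the article does not simply leave missing data to a later plan. It places the decision after inspection of the data, by a group that holds the full database in an open trial, and it does not require that inspection to be blind to allocation. That leaves room for a choice influenced by the results.

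Second, the described method (MCD) suits this outcome poorly. The trial asks whether deterioration can be prevented or delayed, starting from people who are independent. A single median pooled over both arms ignores the arm, the covariates and the 6-month value. When most completers are unchanged, it records every dropout as unchanged too. The arm that loses more people then looks better for that reason alone. At stake are the estimate and the error rate for the primary outcome.

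**Working it through.** **Inputs.** From the article: 65 per group, two-sided 0.05, ADL as primary outcome, entry independent in daily activities, imputation by the median change of all completers. Assumed, because the article gives neither: the share who decline and the dropout rates.

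**The plan's own figure.** The 65 per group rests on the Berg balance scale (32 vs 28, SD 8, 80% power): n = 2 × (1.96 + 0.84)² × (8/4)² ≈ 63, or 64 with the t distribution. The stated 65 reproduces to within two people and is not in dispute. It is used below only as the arm size.

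**Formula.** Let p be the share who decline and d the share missing, unrelated to outcome. If fewer than half of completers decline, the median change is 0 and the share scored as declined is p(1 − d). Differences are control minus intervention, so positive values favour the intervention.

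**No true effect, p = 30% in both arms**
- Dropout 10% control, 30% intervention: 0.30 × 0.90 − 0.30 × 0.70 = 0.27 − 0.21 = 6 points. For the z-test, SE = √(0.24 × 0.76 × 2/65) = 0.075, so the statistic is shifted by 0.06/0.075 = 0.80. Simulated type I error is 12.5%. A Mann-Whitney run on ADL change, with two grades of decline and some improvers, gives 8.1%.
- Dropout 15% and 25%: 0.255 − 0.225 = 3 points; type I error 7.3% (z-test) or 6.1% (Mann-Whitney).
- Dropout 20% in both: no difference; 4.8% (Mann-Whitney).
- Complete-case error stays between 4.3% and 5.5% across the Mann-Whitney scenarios with dropout unrelated to outcome.

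**True effect, 35% vs 15%, 20% missing in both arms.** MCD gives 0.35 × 0.80 − 0.15 × 0.80 = 0.28 − 0.12 = 16 points instead of 20. Simulated power is 63.5%, against 66.9% for complete cases.

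**Same true effect, missing in 40% of decliners and 10% of others**
- MCD: 0.35 × 0.6 − 0.15 × 0.6 = 0.21 − 0.09 = 12 points.
- Complete cases: 0.21/(0.21 + 0.65 × 0.9) − 0.09/(0.09 + 0.85 × 0.9) = 0.264 − 0.105 ≈ 16 points. The promised comparison is itself off by 4.

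**Dropouts who fare worse, with unequal dropout.** Let 30% of completers and 70% of dropouts decline, with dropout 10% control and 30% intervention. Truth: control 0.9 × 0.3 + 0.1 × 0.7 = 34%, intervention 0.7 × 0.3 + 0.3 × 0.7 = 42%, so the intervention is 8 points worse. MCD shows it 6 points better; complete cases show no difference.

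**Where the direction reverses.** If 60% decline, the median lies above 0 in about 98% of runs and dropouts are scored as declined. With dropout 10% and 30%: (0.54 + 0.10) − (0.42 + 0.30) = −8 points, now against the intervention.

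**Cost of a choice driven by results.** With no effect and 20% dropout in both arms, taking the smallest p-value from MCD, complete cases and a worst-case imputation raises type I error to 8.4%.

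**The case against.** The strongest reply is that MCD is not the plan. It is offered as one candidate, others will be considered, a statistician is consulted, and the details of imputation ordinarily belong in an analysis plan that is not shown. All of that stands. A reader might infer that the primary estimate is biased as planned; the documents do not support this, because the bias arises only if MCD is chosen.

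A reader might also infer that the method will be picked by people who have seen outcomes by arm. The article does not say so. Examining the characteristics of the data could mean only the amount and pattern of missing values, and nothing is said about whether the analyst is blinded. What remains is that blind examination is not promised, while access and timing leave the other course open.

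Scoring dropouts as unchanged needs a median ADL change of 0. The entry criterion makes that plausible, but it is not stated, and a value based on the median leaves the exact rule open. A false effect also needs unequal dropout.

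The promised complete-case comparison would expose the artefact when dropout is unrelated to outcome. It does not test for dropouts who did worse.

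Finally, it is tempting to charge MCD with the whole fall in power from 76% with full data to about 63%. Most of that comes from the missing data: against complete cases MCD costs 66.9 − 63.5 = 3.4 points.

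**Conclusion.** The concern holds in a limited form. The article fixes the timing of the missing-data choice badly, and the one imputation method it describes is a poor candidate for the primary outcome.

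If MCD were used and fewer than half of completers declined, a true difference would shrink by about the missing share (20 points to 16 at 20% missing). A false difference would appear when dropout differs: 3 points for a gap of 10 percentage points and 6 points for a gap of 20, with type I error of 6 to 7% and 8 to 12.5% respectively, depending on the test and the assumed ADL distribution. With equal dropout the error rate holds.

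These sizes rest on assumed rates of decline and dropout. This should be fixed, but it does not invalidate the plan, because MCD is not a commitment.

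**What to change.** In the Statistical analyses section, name the primary missing-data method for ADL and state that it is settled before anyone sees outcomes by arm. Either of two standard choices would serve: a likelihood-based ordinal repeated-measures model on the baseline, 6- and 12-month values, or multiple imputation carried out separately by arm using the baseline and 6-month values. Drop MCD, or keep it only as a sensitivity analysis. Keep the complete-case comparison and add an analysis in which dropouts are assumed to have done worse than completers by a stated amount.

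The cost is a few sentences, some programming, and the loss of direct comparability with the preceding study's method; keeping MCD as a sensitivity analysis preserves much of that. Neither replacement was simulated here. Both rely on dropout being explained by the observed values, which is why the added sensitivity analysis is needed.

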**Planned flow of participants in the Promoting Aging Migrants’ Capabilities Study.**

The invitation process and data collection are conducted by trained research assistants and conducted in the language preferred by the participant. The standardised baseline assessment comprises an interview, measurements, and observation. Follow-up data, identical to the baseline assessment except for demographics, will be collected in both groups at 6- and 12 months after the intervention. The complete data collection form, as well as consent and participant information forms, can be retrieved by contacting the first author (SG) or last author ([name]). In addition, information on reasons for any non-adherence (e.g. discontinuation of intervention) and non-retention (i.e. consent withdrawn or lost to follow-up) will be collected. Data from municipal registers will also be obtained and used to study care consumption.

The recruitment of participants began in autumn 2012 and is planned to be completed by the end of December 2014. The intervention began at the same time as the inclusion, and will be completed no later than 6 months after the last inclusion. The 12-months follow-up will be completed in January 2016. A detailed study timeline is shown in Table 4.

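### The one named missing-data check, a comparison with complete cases, says little about whether dropouts fared worse in one arm than in the other

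*Protocol article*

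**What the plan says.** All of this is in the protocol article.

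- **Analysis principle.** Under Statistical analyses, the trial follows intention to treat: "participants will be analysed on the basis of the group to which they were randomised".
- **Main method.** It is not fixed. One option is described, taken from the preceding trial, in which "a missing value was imputed with a value based on the median change of deterioration (MCD) between two measuring points". The change comes from the records "of all those who participated at both measuring points", that is, from completers. No split by arm is stated, so it is read here as pooled. The section adds that "other methods of handling missing data will also be considered, and a final decision will be made by the lead researcher", with a statistician consulted.
- **Sensitivity analysis.** One comparison is fixed, whichever main method is adopted: "sensitivity analyses will be performed to compare the results to complete case analyses". No other missing-data sensitivity analysis is named.
- **Reasons for loss.** The data-collection text after Figure 1 says that reasons will be recorded for "non-retention (i.e. consent withdrawn or lost to follow-up"). Death is not listed separately, and no missing-data analysis is said to use these reasons.

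**The concern.** A sensitivity analysis for missing data is useful when it changes the assumption that matters most. Here that is the assumption that participants who leave did about as well as those who stay. Complete-case analysis makes it within each arm. MCD makes it by giving every missing participant a completers' change. Neither lets dropouts do worse.

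The article gives reasons to take this seriously. The hypothesis is about delaying deterioration, so decline is both the outcome and a plausible cause of leaving. The Background links frailty to institutional care and mortality. Under Ethical considerations, a shortened form is offered to participants who struggle, so some values will be missing because of participants' condition. Participants, professionals and assessors are unblinded, and only one arm attends four meetings and a home visit, so loss that differs by arm is plausible, though not shown.

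If declining participants left the intervention arm more often than the control arm, an apparent ADL benefit could appear in both the main analysis and its check.

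**Working it through.** **1. The plan's own figure.** The Power calculation uses the Berg balance scale: difference 32 − 28 = 4, SD 8, two-sided 0.05, 80% power. Per arm, n = 2 × (1.96 + 0.84)² × 8² / 4² ≈ 63, or 64 with the t distribution. The stated 65 is reproduced, with power about 81%. The checks below use 65 per arm.

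**2. Expected rates on a deteriorated / not deteriorated ADL outcome.** Assumed, because the article gives no values: 25% truly deteriorate in both arms, 15% drop out per arm, and a share f of intervention dropouts had deteriorated. Control dropout is random (f = 0.25). Per 100 randomised:

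- Complete case: (25 − 15f) / 85
- MCD, median change 0 (missing counted as not deteriorated): (25 − 15f) / 100
- MCD, imputed change counted as deterioration: (25 − 15f + 15) / 100

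| Intervention f | Complete case | MCD, change 0 | MCD, counted as deteriorated |
|---|---|---|---|
| 0.50 | 17.5/85 = 20.6% v 25.0% | 17.5% v 21.3% | 32.5% v 36.3% |
| 0.75 | 13.75/85 = 16.2% v 25.0% | 13.8% v 21.3% | 28.8% v 36.3% |

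The true difference is zero, yet every cell favours the intervention. The two MCD columns show the same absolute gap, but the last has higher rates and so more variance.

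**3. How often both analyses show a significant false benefit.** Simulation with a pooled z test, two-sided 0.05, counting results in favour of the intervention:

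- Random dropout in both arms, median change 0: about 2%.
- f = 0.50 in the intervention arm only: 6.6% (change 0) or 4.1% (counted as deteriorated).
- f = 0.75 in the intervention arm only: 18.0% or 10.9%.
- f = 0.50 or 0.75 in both arms: about 1% to 2%.

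With median change 0, the two significance verdicts agree in 99%, 98% and 95% of trials as f goes from 0.25 to 0.50 to 0.75 in the intervention arm. Agreement barely falls while the false-benefit rate rises about ninefold.

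**4. Cross-check on a continuous score.** 4,000 trials per scenario, SD 8 assumed for change, completers' effect 4, MCD from the pooled median:

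| Dropout, intervention v control | Dropouts' unseen change | Full data | Complete case | MCD | Same verdict |
|---|---|---|---|---|---|
| 20% v 20% | 8 worse, intervention only | 2.37 | 3.96 | 3.16 | 99.3% |
| 30% v 10% | 8 worse, both arms | 2.40 | 4.00 | 3.14 | 97.0% |
| 30% v 10% | 16 worse, both arms | 0.82 | 4.03 | 3.17 | 97.2% |
| 20% v 20% | 8 worse, both arms | 4.02 | 4.02 | 3.21 | 99.4% |

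In the first three rows both analyses overstate the full-data effect and still agree on significance. In the last row complete case is unbiased. MCD is lower there only because a pooled median shrinks the difference by roughly the dropout share (4.0 × 0.8 = 3.2).

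**The case against.** Comparing an imputed analysis with complete cases is ordinary practice, and the sentence is not wrong in itself. The article is condensed, and a separate analysis plan may add further analyses. That is why the point is confined to the comparison the article does fix, which applies whatever main method is chosen.

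Four stronger readings are tempting, and the documents do not support them.

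- *Agreement is built in.* A reader might infer this from MCD, but MCD is only one option. A method with a different assumption could depart from complete cases, although the text commits to none. Even with MCD, the likeness lies in the significance verdict, not the estimate. If the imputed change counts as deterioration, then at f = 0.75 MCD confirms only about 53% of complete-case false positives (10.9% of 20.6%), so the comparison discriminates to some extent.
- *Any loss of frailer participants biases the result.* With equally frequent and equally informative dropout in both arms, the false-benefit rate stays at about 1% to 2%. Follow-up assessments are the same in both arms, and no dropout figure in the article shows a difference.
- *The authors would present agreement as proof of robustness.* They do not say so.
- *Deaths are mishandled.* The wording on non-retention describes data collection and is not an analysis rule. Placing deaths in the worst ADL category is one estimand choice among several.

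What stands is that neither complete case nor the one described imputation probes outcomes that are worse among dropouts in one arm.

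**Conclusion.** The point holds in limited form. The one missing-data check the article names cannot be relied on to reveal dropouts who fared worse in one arm than in the other, because complete case and MCD both rest on completers. Under the assumed one-sided scenario, a false benefit passes both analyses in about 6.6% to 18% of trials with median change 0, and about 4% to 11% if imputed participants count as deteriorated. The nominal one-sided rate is 2.5%. Without a difference between arms there is no excess.

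The 15% dropout, the 25% deterioration, the values of f, the two-category ADL outcome and the pooled reading of MCD are all assumptions. The direction of the result does not need the exact values, but the size does. This is a worthwhile strengthening of the safeguard for the primary conclusion. It does not show that the conclusion will be wrong.

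**What to change.** In Statistical analyses, keep the complete-case comparison as description and add an arm-specific tipping-point (delta-adjusted) sensitivity analysis of the primary ADL outcome. Missing participants are assigned progressively worse ADL, separately by arm, and the report states the shift at which the conclusion changes. From the non-retention reasons already being collected, report deaths and moves to institutional care by arm. How deaths enter the analysis is for the trial's statistician to decide and state in advance.

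The cost is a sentence or two of text and a few extra runs, with no new participants or visits. The downside is that a fragile result will be shown to be fragile.
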